## 2. OBJECTIVES

In this multicenter prospective randomised low intervention clinical trial, we aim to investigate if the use of weekly low dose cisplatin can increase the compliance to the planned chemotherapy scheme in LA-HNSCC patients with low SMM to a level of compliance to three-weekly high dose cisplatin of patients without low SMM. We hypothesize that in LA-HNSCC patients with low SMM undergoing concurrent primary CRT weekly with low dose cisplatin compliance rate to planned chemotherapy scheme improves from 55.7% to 86.3%. The primary outcome of this study is the difference in compliance (defined as absence of CDLT) rate to the proposed cisplatin scheme between weekly low dose cisplatin and three-weekly high dose cisplatin in patients with low SMM. Secondary outcomes of this study are treatment cumulative cisplatin dose, acute and late adverse events (AE's), time to recurrence, 2-years survival, quality of life, costs and patient's preference.

### Primary Objective:

- To compare the compliance rate to proposed cisplatin scheme between weekly low dose cisplatin or three-weekly high dose cisplatin in patients with low SMM.

### Secondary Objective(s):

- To investigate whether weekly low dose cisplatin can increase the compliance to the planned chemotherapy scheme in LA-HNSCC patients with low SMM to a level of compliance to three-weekly high dose cisplatin of patients without low SMM.
- To investigate treatment cumulative cisplatin dose in patients with low SMM receiving weekly low dose or three-weekly high dose cisplatin.
- To investigate acute and late adverse events/toxicity in patients with low SMM receiving weekly low dose or three-weekly high dose cisplatin.
- To investigate time to recurrence in patients with low SMM receiving weekly low dose or three-weekly high dose cisplatin.
- To investigate 2-years survival in patients with low SMM receiving weekly low dose or three-weekly high dose cisplatin.
- To investigate quality of life in patients with low SMM receiving weekly low dose or three-weekly high dose cisplatin.
- To investigate costs in care for patients with low SMM receiving weekly low dose or three-weekly high dose cisplatin.
- To investigate patient's preference of treatment in patients with low SMM receiving weekly low dose or three-weekly high dose cisplatin.

### 3. STUDY DESIGN

In this multicenter prospective randomised low intervention clinical trial, the compliance of weekly low dose cisplatin with concurrent radiotherapy in LA-HNSCC patients with low SMM will be investigated. SMM will be measured on routinely performed (PET-)CT or MRI scans before the multidisciplinary head and neck cancer meeting by the treating physician. Patients who are found eligible by the multidisciplinary team and are planned for cisplatin based concurrent CRT will be asked to participate in this study by the investigator. Seventy patients with low SMM will be randomised between weekly low dose and three-weekly high dose cisplatin. To assure the inclusion of seventy patients with low SMM, 129 patients in total are needed as explained in paragraph 4.4. Therefore 59 patients with normal skeletal muscle mass will be asked to participate as well. They will receive the most standard cisplatin scheme for the centre they are admitted to specifically and will be included in follow-up. Baseline characteristics and outcomes will be collected for all patients.

SMM will be estimated using a validated technique based on measurement of the cross-sectional area of the sternocleidomastoid muscle and paravertebral muscles on the level of C3 on routinely performed CT or MRI. In patients who underwent fluorodeoxyglucose-positron emission tomography(FDG-PET)/CT as part of the diagnostic work-up, as a control of SMM measurement at the level of C3, SMM will also be measured at the level of L3, which is the most commonly used method in medical literature as a control of SMM measurement at the level of C3.

Based on the cut-off value calculated by Wendrich et al., low SMM is defined as skeletal muscle mass  $\leq 43,3 \text{ cm}^2/\text{m}^2$ . Patients with low SMM will be randomised between weekly low dose cisplatin and three-weekly high dose cisplatin with concurrent RT. The rate of compliance to proposed cisplatin scheme will be compared between three groups: patients with low SMM with weekly low dose cisplatin, patients with low SMM and three-weekly high dose cisplatin and the rest group of normal SMM receiving the local standard scheme, which is three-weekly 100 mg/m^2 cisplatin in the UMC Utrecht, Noordwest Ziekenhuisgroep, Leiden University Medical Center, and VUmc, and weekly 40 mg/m^2 cisplatin in the NKI-AVL.

During chemoradiation, all patients will be frequently seen by their radiotherapist and oncologist. It is conform standard procedures to document toxicities and the researcher will collect data and add it to the database. Follow-up will consist of clinical examination every two months in the first year and every three months in the second year, for at least 24 months after treatment which is conform standard procedures. Low SMM patients will be asked to answer the EORTC QLQ-C30, EORTC-QLQ-H&N35, EQ-5D-5L and PCQ questionnaires before and 3, 6, 12 and 24 months after end of CRT. Normal SMM patients will be asked to answer the EORTC QLQ-C30, EORTC-QLQ-H&N35, EQ-5D-5L questionnaires before and 3, 6, 12 and 24 months after CRT. Questionnaires will initially be send by e-mail using Castor (EDC), but on patient's or treating physicians request paper questionnaires are available as well. Paper questionnaires will be transmitted to Castor EDC by the

executive researcher or (delegated by) the principal investigator. Patients' experience will be explored three months after CRT by qualitative research using semi-structured interviews. Semi-structured interviews will be analyzed by two investigators using thematic descriptive analyses. A cost-effectiveness analysis will be performed to compare three-weekly and weekly cisplatin treatment. Time interval between inclusion and end of treatment patient will be approximately two months, total time of follow-up will be 24 months after end of treatment. After follow-up, 6 months will be given for analysis and final report. The end of treatment is defined as the day of the last radiation session and is consistent for all groups.

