## 4. STUDY POPULATION

### 4.1 Population (base)

Patients with LA-HNSCC who are planned for cisplatin based primary concurrent CRT (as standard of care) in one of the participating centers of the Dutch Head and Neck Society will be asked to participate in this study. In the Netherlands yearly 250 LA-HNSCC are treated with primary CRT and in a previous study 54.5% patients had low SMM.

SMM will be estimated based on measurement of the cross-sectional area of the sternocleidomastoid muscle and paravertebral muscles on the level of the third cervical vertebrae (C3) on routinely performed CT or MRI. In patients who undergo FDG-PET/CT as part of the routine diagnostic work-up, as a control of SMM measurement at the level of C3, SMM will also be measured at the level of the third lumbar vertebra (L3), which is the most commonly used method in medical literature as a control of SMM measurement at the level of C3.

Seventy patients with low SMM will be randomised between low-dose weekly and high-dose three-weekly cisplatin therapeutic scheme with concurrent radiation. 59 patients with normal SMM will also be asked to participate in this study and will receive the standard of care of the centre they are admitted to (either three-weekly 100 mg/m^2 or weekly 40 mg/m^2 cisplatin). If 129 patients are included, but the minimum of 70 patients with low SMM is not yet reached, we will include additional patients until 70 patients with low SMM are included, in order to create sufficient power for statistical analysis. See paragraph 4.4 for the exact calculation.

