#### 4.4 Sample size calculation

In the retrospective study by Wendrich et al., out of 112 patients 30.4% experienced CDLT (meaning compliance to chemotherapy regimen was 69.6%). Using a cut-off 43.2 cm^2/m^2, 54.5% patients had low SMM. Patients with low SMM experienced CDLT more frequently than patients with normal SMM (44.3% vs. 13.7%,  $p < 0.001$ ). Thus compliance rates to chemotherapy regimen were 55.7% and 86.3%, respectively. We hypothesize therefore that in patients with low skeletal muscle mass and weekly low dose cisplatin, also 86.3% compliance will be reached. If we compare this compliance to an expected compliance of 55.7% in the arm of with a three-weekly high dose cisplatin, 33 patients with low SMM per arm are needed to show that the compliance in the weekly low dose cisplatin scheme is statistically significantly better than the threeweekly high dose scheme (two-sided alpha 0.05 and power 80%). With an expected drop-out of 5% 70 patients with low SMM are needed. Power calculations were done using PASS software. Since 54.5% of patients undergoing cisplatin based concurrent CRT have low SMM, to find the 70 patients with low SMM a total of 129 LA-HNSCC patients undergoing cisplatin based concurrent CRT are needed.

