### 10.2 Secondary study parameter(s)

Treatment toxicity is assessed with the Common Toxicity Criteria Adverse Events (CTCAE) v5.0 for a period of 24 months from the end of treatment. Toxicity scored as CDLT by the treating physician will be assessed, clarified if necessary, and reconfirmed separately. A severe toxic event is defined as a toxicity assessed as grade 3–5. Toxicities are classified as acute if they first appeared during or up to 3 months after treatment, and are classified as late if they persist, or first appear, more than 3 months after treatment. Multiple occurrences of events of a single toxicity type within an analysis time period are counted as a single event. Median numbers of toxicity events per patient (short-term [acute] toxicity and adverse long-term [late] effects, based on the TAME method of reporting toxicities) are compared between trial arms using t-tests. Proportions of patients affected by one or more toxicity event are compared between trial arms using Fishers exact test. Total administered cisplatin dose will also be recorded and means (or medians depending on the distribution) compared between trial arms.

Overall survival, disease-specific survival, loco-regional recurrences and time to recurrence are measured from the starting date of chemotherapy and compared between the three groups by the log-rank test with all-cause mortality in the intention-to treat population. Deaths are classified as being due to head and neck cancer or to other causes. Recurrences can be loco-regional or distant, or both. Patients who died from head and neck cancer causes as the first event are classed as recurrences. Patients on follow-up and patients lost to follow-up are censored at the last date at which they were known to be alive. Total time of follow-up per patient is two years. Hazard ratios and 95% CIs are generated with a univariate Cox proportional hazards model. The Schoenfeld residuals are tested by plotting the observed Kaplan- Meier values against the Cox predicted values. The effect of randomised treatment on outcome is also assessed after adjusting for known prognostic factors with a multivariate Cox proportional hazards model. At 3 months after treatment semi-structured interviews are conducted to obtain a better understanding of the patients' experience and preference for the treatment schemes, until saturation is reached. Semi-

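### Compliance and survival are to be compared across three groups, one of them non-randomised and on mixed schedules, although the objectives and sample size concern the two randomised low-SMM arms; the benchmark group is mis-specified.

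*Protocol*

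**What the plan says.** **Two-arm statements.** The primary objective in Section 2 is "To compare the compliance rate to proposed cisplatin scheme between weekly low dose cisplatin or three-weekly high dose cisplatin in patients with low SMM". Section 2 defines the primary outcome as the same contrast and words the time-to-recurrence and 2-year-survival objectives within low SMM. Section 4.4 sizes only this contrast, and Section 8.2 randomises only low-SMM patients, 1:1.

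**Three-group statements.** Section 3: "The rate of compliance to proposed cisplatin scheme will be compared between three groups". These are low SMM on weekly, low SMM on three-weekly, and normal SMM on the local standard. Section 10.2 has overall survival, disease-specific survival, loco-regional recurrence and time to recurrence "compared between the three groups by the log-rank test with all-cause mortality in the intention-to treat population".

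**The third group.** Section 4.1: "59 patients with normal SMM will also be asked to participate in this study and will receive the standard of care of the centre". According to Sections 3 and 6.6, that standard is three-weekly in four named centres and weekly in one. Section 8.1.1 gives weekly regimens their own definition of CDLT, the event whose absence counts as compliance.

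**The benchmark.** A secondary objective in Section 2 asks whether weekly treatment can raise compliance in low SMM "to a level of compliance to three-weekly high dose cisplatin of patients without low SMM". The Summary gives this as the trial's only objective.

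**The concern.** The protocol's premise is that muscle mass predicts CDLT on three-weekly cisplatin. A test that sets normal-SMM patients beside the two low-SMM arms can therefore be significant because of muscle mass, even when the schedules perform identically. Section 10.1 names the outcome and the analysis population, but neither the arms nor the test. The sentence in Section 3 is thus the most explicit account of how compliance will be compared, and it does not match the objective. For survival and recurrence the mismatch is plainer: Section 10.2 prescribes a three-group log-rank test in an intention-to-treat population, although one group was never randomised.

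The benchmark has a separate problem. The objective refers to three-weekly treatment in patients without low SMM, whereas the planned third group mixes two schedules and two CDLT rules. Its pooled rate is not the rate named.

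**Working it through.** **Inputs from the protocol.** Section 4.4: "Thus compliance rates to chemotherapy regimen were 55.7% and 86.3%, respectively" (low and normal SMM, from the earlier retrospective cohort); the weekly arm is assumed to match the normal-SMM rate ("in patients with low skeletal muscle mass and weekly low dose cisplatin, also 86.3% compliance will be reached"); "two-sided alpha 0.05 and power 80"%; 33 per arm; 5% drop-out; low-SMM prevalence 54.5%. Sections 3 and 4.1: 70 randomised and 59 with normal SMM. Group sizes are therefore 35/35/59.

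**1. The sample size is for two arms.** With p1 = 0.557, p2 = 0.863 and mean 0.710:

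n = [1.96·√(2·0.710·0.290) + 0.842·√(0.557·0.443 + 0.863·0.137)]² / 0.306² = 33.3 per arm.

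This reproduces the stated 33; power at 33 per arm is 79.6%. Then 66/0.95 = 69.5, so 70, and 70/0.545 = 128.4, so 129. No three-group comparison enters.

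**2. A three-group test with no treatment effect.** Assume a Pearson chi-square on 2 df, both randomised arms at 55.7% and normal SMM at 86.3%.

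- Pooled rate: (70·0.557 + 59·0.863)/129 = 0.697.
- Statistic if the observed rates equal these: [70·(0.557 − 0.697)² + 59·(0.863 − 0.697)²]/(0.697·0.303) ≈ 14.2, against a critical value of 5.99.

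Rejection rates at 0.05, by simulation (200,000 trials per row):

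| Normal-SMM compliance | Three-group test, identical randomised arms |
|---|---|
| 86.3% (protocol) | about 95% |
| 80% (assumed) | about 77% |
| 75% (assumed) | about 54% |
| 70% (assumed) | about 31% |
| 65% (assumed) | about 15% |

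The two-arm chi-square in randomised patients (35 vs 35) rejects in about 4.5% of trials with no effect. It has about 83% power under the planned effect.

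**3. The benchmark.** The share of the 59 treated weekly is not stated. Assume 10% to 50%.

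- Left on three-weekly: 59·0.9 ≈ 53, down to 59·0.5 ≈ 30.
- Pooled rate at a 50% share, with three-weekly compliance 86.3% and weekly compliance assumed between 75% and 95%: 0.5·0.863 + 0.5·0.75 = 80.6%, up to 0.5·0.863 + 0.5·0.95 = 90.6%. The pooled rate can therefore miss the named benchmark in either direction.
- 95% CI half-width for the difference between the three-weekly subset (m patients) and the 35-patient weekly arm, both at 86.3%: 1.96·√[0.863·0.137·(1/m + 1/35)]. This is 14.7 points at m = 53 and 16.8 points at m = 30.

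**4. What a non-significant benchmark comparison shows.** If weekly compliance in low SMM were truly 75% (assumed) against 86.3%, with 35 vs 59 patients, a two-sided chi-square would be non-significant in about 71% of trials. Non-significance is therefore weak evidence that the level has been reached.

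**The case against.** The strongest reply is that the primary inference is already two-arm. The primary outcome, primary objective and sample size all say so. Section 10.2 compares toxicity and cumulative dose between trial arms and estimates the effect of randomised treatment with an adjusted Cox model. This stands: the two-arm analysis is available and adequately sized, and what is at fault is the wording that departs from it.

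Second, no omnibus test is named for compliance. Section 10 lists several tests without assigning one, and pairwise comparisons would fit Section 3 equally well. This also stands, so the 95% is conditional on a 2-df test. It is the power to detect a muscle-mass difference, not the error rate of the primary test. It also applies a rate from a cohort treated three-weekly to a group on mixed schedules, which is why the range in the table matters.

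Third, for survival the protocol links shorter survival to CDLT, not directly to muscle mass, and gives no normal-SMM survival rate. The size of the problem there cannot be computed. The contradiction in Section 10.2 remains, because the three-group log-rank test is explicit.

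A reader might infer that the benchmark does not exist in this trial. The documents do not support that: normal-SMM patients are treated three-weekly at four of the five named centres, so the group can be formed as a subset. A reader might also take the benchmark objective as a formal non-inferiority claim that requires a margin. It is a secondary objective, nothing says that a non-significant difference will be taken as success, and with a half-width near 15 to 17 points a margin would be of doubtful use.

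**Conclusion.** The point holds as a should-fix. Sections 3 and 10.2 prescribe three-group comparisons that do not answer the two-arm questions in Section 2, and Section 10.2 applies intention-to-treat to patients who were not randomised. If compliance were tested across the three groups on 2 df, identical randomised arms would still give a significant result in about 95% of trials at the protocol's rates. Over assumed normal-SMM compliance of 65% to 80%, the figure is 15% to 77%. The benchmark is mis-specified, not absent. A reader might conclude that the primary analysis is invalid; that goes too far, because the primary outcome definition, the allocation and the sample size are sound for the two-arm test.

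**What to change.** 1. In Sections 3 and 10.2, state that tests of treatment effect for compliance, survival and recurrence use only the two randomised low-SMM arms. Limit intention-to-treat to randomised patients.
2. For the benchmark objective, compare the low-SMM weekly arm with normal-SMM patients treated three-weekly only. Label the comparison non-randomised and descriptive, report the difference with a 95% CI, and state that a non-significant difference will not be read as having reached the level. Report normal-SMM patients on weekly treatment separately.
3. Align the Summary objective with the primary objective in Section 2.

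The cost is wording; enrolment, treatment and sample size do not change. The downside is a benchmark group smaller than 59 (about 30 to 53 under the assumed weekly shares), with a difference known only to within about 15 to 17 points.

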#### **6.6 Dosages, dosage modifications and method of administration**

The intervention arm will receive 40 mg/m^2 cisplatin weekly during seven weeks. The control arm will receive 100 mg/m^2 cisplatin every three weeks for three cycles in the UMCU, Noordwest Ziekenhuisgroep, Leiden University Medical Center, and VUmc. Patient with a normal SMM in the AVL, will receive 40 mg/m^2 cisplatin weekly during seven weeks, since this is the standard treatment for the AVL. Administration is standardized for cisplatin and consists of intravenous cisplatin solution slowly (approximately four hours) injected.

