## 8. METHODS

### 8.1 Study parameters/endpoints

#### 8.1.1 Main study parameter/endpoint

The primary outcome parameter is compliance (non CDLT) rate to the proposed cisplatin scheme. Compliance to chemotherapy is defined as the absence of CDLT. CDLT is defined as any toxicity resulting in a cisplatin dose-reduction of  $\geq 50\%$ , a postponement of treatment of  $\geq 4$  days or a definite termination of cisplatin after the first or second cycle of therapy. For weekly cisplatin regimens CDLT is defined as skipped cisplatin treatments or a definite termination of cisplatin before all scheduled cycles of therapy are given.

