## 8.3 Study procedures

All patients diagnosed with an indication for primary CRT, will be identified and screened for eligibility at a weekly multidisciplinary head and neck oncology meeting. SMM will be measured on routinely performed pre-treatment (PET-)CT or MRI of the head and neck. During the multidisciplinary meeting, it will be decided whether the patient has an indication for primary CRT. If the patient is considered for cisplatin CRT, the investigator will inform the patient about the study and asked to sign informed consent. Patients with normal or high SMM (>43.2 cm^2/m^2) will receive the standard cisplatin scheme, which differs per centre. This will either be three-weekly high-dose cisplatin of 100 mg/m^2 or a weekly low-dose cisplatin of 40 mg/m^2. Patients with a low SMM ≤43.2 cm^2/m^2 will be randomised for either low- or high-dose cisplatin, respectively 40 mg/m^2 or 100 mg/m^2. Dependent on each centre, the local pharmacy or the local pharmacy and study pharmacy will be involved since treatment with cisplatin is standard of care and the planned cumulative dosage for both groups will be comparable.

The 100 and 40 mg/m^2 schemes differ in dose and frequency, but also in administration: three times hospital admission versus 7 day visits at the (outpatient) clinic. Because every patient receives radiotherapy daily (which is part of the standard of care), no additional hospital visits are required. In case of CDLT, the treating physician will decide which therapy is most suitable to the patient. It is conform standard guidelines to switch to different type of therapy when cisplatin has become too toxic. There will be no cross-over from the high to low-dose group, since this is against standard of care in which cisplatin therapy is stopped and carboplatin is given instead. The data will still be eligible for analysis in this research. During treatment, the patient will frequently be seen by the treating radiotherapist and oncologist. Adverse events, such as toxicities and CDLT are reported in the EPR according to standard hospital guidelines. Two to three days after each cisplatin dose, the kidney function will be determined. The investigator will collect clinical relevant data for each week of treatment. Data collected include CDLT, cause and type of acute toxicity, grade of toxicity according to Common

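### The first secondary objective sets three-weekly normal-SMM patients as the benchmark, but Section 3 compares against a normal-SMM group that also contains weekly-treated patients from one centre

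*Protocol*

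**What the plan says.** The first secondary objective (Section 2) asks whether weekly cisplatin can raise compliance in low-SMM patients "to a level of compliance to three-weekly high dose cisplatin of patients without low SMM". The Summary objective, the end of Section 1 and the opening of Section 2 name the same benchmark: normal SMM, three-weekly scheme.

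Section 3 describes the comparison. "The rate of compliance to proposed cisplatin scheme will be compared between three groups": low SMM on weekly, low SMM on three-weekly, and "the rest group of normal SMM receiving the local standard scheme". It then lists four centres where that standard is three-weekly and one, the NKI-AVL, where it is weekly. Section 8.3 repeats that normal-SMM patients "will receive the standard cisplatin scheme, which differs per centre". Section 6.6 says of the fifth centre: "Patient with a normal SMM in the AVL, will receive" the weekly scheme, "since this is the standard treatment for the AVL". Section 4.1 also allows either scheme.

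On numbers, Section 3 says: "Therefore 59 patients with normal skeletal muscle mass will be asked to participate as well". It does not divide the 59 by scheme or centre. Section 10.2 compares survival and recurrence across the three groups, again without a split.

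**The concern.** The objective names one population and the design section compares against another. Among normal-SMM patients the scheme is decided by the centre, so a pooled compliance rate mixes two regimens and cannot separate regimen from centre. It also depends on how many normal-SMM patients the weekly centre happens to recruit, which has nothing to do with the question.

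The 86.3% behind the hypothesis comes from a retrospective cohort treated with three-weekly cisplatin only (Sections 1 and 4.4). A pooled group is therefore not the population from which the expectation was taken. At stake is the interpretation of the first secondary objective, which is also the only objective stated in the Summary and so likely to be reported prominently.

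**Working it through.** **1. The plan's own figures.**
- Normal-SMM compliance: 100 - 13.7 = 86.3%. Low-SMM compliance: 100 - 44.3 = 55.7% (Section 4.4).
- Sample size for 55.7% versus 86.3%, two-sided alpha 0.05, power 80%: the pooled-variance formula gives 34 per arm against the stated 33, and 33 per arm gives 79.6% power. This is close enough and does not bear on the point.
- Drop-out: 66/0.95 = 69.5, so 70. Total: 70/0.545 = 128.4, so 129. Normal SMM: 129 - 70 = 59.

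**2. The two definitions side by side.**

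| | Objective (Summary, Section 2) | Compared group (Section 3) |
|---|---|---|
| Muscle mass | normal | normal |
| Scheme | three-weekly | three-weekly at four centres, weekly at one |
| Source of 86.3% | three-weekly cohort | not matched |

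The pooled rate estimates the stated benchmark only if the weekly centre contributes no normal-SMM patients, or if weekly compliance in normal SMM also happens to be 86.3%.

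**3. Size of the shift.** Let w be the share of normal-SMM patients on weekly treatment and p their compliance. The documents give neither.

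Pooled rate = (1 - w) × 0.863 + w × p

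Assume w = 20-40%. For p, take 70% as an assumption and 88%, the weekly adherence from the systematic review cited in Section 1.

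| w | p = 70% | p = 88% |
|---|---|---|
| 20% | 0.6904 + 0.1400 = 83.0% (-3.3 points) | 0.6904 + 0.1760 = 86.6% (+0.3) |
| 40% | 0.5178 + 0.2800 = 79.8% (-6.5 points) | 0.5178 + 0.3520 = 87.0% (+0.7) |

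**4. Precision if the reference group is restricted.** At w = 20-40%, 12-24 of the 59 drop out of the reference group, leaving 47-35. Take 86.3% in both groups and 35 low-SMM patients on weekly treatment (half of 70).

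SE of one group = √(0.863 × 0.137 / n). SE of the difference = √(0.863 × 0.137 × (1/n + 1/35)).

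| n in reference group | SE of benchmark | SE of difference |
|---|---|---|
| 59 | 4.5 points | 7.3 points |
| 47 | 5.0 points | 7.7 points |
| 35 | 5.8 points | 8.2 points |

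**5. Restricting both groups to the four centres.** If the low-SMM weekly arm has the same 20-40% share at the fifth centre, it falls from 35 to 28-21, and the SE of the difference becomes √(0.118231 × (1/47 + 1/28)) = 8.2 points to √(0.118231 × (1/35 + 1/21)) = 9.5 points.

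**The case against.** The strongest reply is that Section 3 lists three groups without saying that the pooled group is the reference for this objective. The objective itself specifies three-weekly patients, and choosing the matching subset could be left to an analysis plan. This has some force, since the link is the natural reading rather than a stated one. But Section 3 positively defines the compared group, and nothing in the protocol restricts it. An analysis plan that did so would depart from Section 3, so the two sections need reconciling in any case.

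The reach is also limited, and this stands. The primary objective and the sample size rest on the randomised comparison within low SMM. The 59 normal-SMM patients are non-randomised and arise from the number needed to find 70 with low SMM.

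Three stronger readings are tempting, and the documents do not support them.
- A reader might infer that pooling makes success easier to claim. The protocol states no margin, test or success rule for having reached the normal-SMM level, so there is no threshold to lower.
- A reader might infer a large downward shift. A 40% share with 60% weekly compliance gives 75.8%, or 10.5 points down, but that needs an extreme choice for both unknowns. The only weekly figure in the protocol, 88%, gives a rise of less than one point. It does not settle the matter either: it comes from a general population, in which three-weekly adherence was 71%, and was not scored under Section 8.1.1.
- A reader might count the two CDLT rules in Section 8.1.1 as part of this problem. The general rule includes "a definite termination of cisplatin after the first or second cycle of therapy", while the weekly rule counts skipped treatments or stopping before all scheduled cycles. Low-SMM weekly patients are scored by the weekly rule whatever the reference group is, so that issue is separate and correcting the reference group leaves it in place.

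**Conclusion.** The mismatch is certain from the text: the objective names normal-SMM patients on three-weekly treatment, and Section 3 compares against a normal-SMM group of mixed scheme. It affects one secondary, non-randomised comparison and leaves the primary comparison untouched. Its numerical effect cannot be determined from the documents. Under the assumed 20-40% weekly share it runs from about 6.5 points down (70% weekly compliance) to 0.7 points up (88%), and the smaller of these shifts lie within the benchmark's own standard error of 4.5 points. The reason to correct it is that the comparison would not answer the stated question, whichever way the shift goes.

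**What to change.** In Sections 3 and 10, state that the reference group for the first secondary objective is normal-SMM patients receiving three-weekly cisplatin. Report the weekly-treated normal-SMM patients separately, as description only. Keep all randomised low-SMM weekly patients from all five centres in the main comparison, and add a comparison limited to the four three-weekly centres as a sensitivity analysis, because scheme and centre coincide in the reference group.

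This changes analysis wording only. It alters no treatment, recruitment or data collection, and is best settled before outcomes are known. The cost is precision: at the assumed share, the benchmark's standard error goes from 4.5 to 5.0-5.8 points and that of the difference from about 7.3 to 7.7-8.2 points. Making the four-centre comparison the main one would cost more (8.2-9.5 points) and set aside randomised patients, which is why it belongs in a sensitivity analysis.

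Rewording the objective to refer to the local standard scheme would also remove the contradiction, but it would change the question and detach it from the three-weekly cohort that supplies the 86.3%. The differing CDLT rules need their own resolution.
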